### Recruitment {15}

Active upper gastrointestinal bleeding without varices is a frequent indication for emergency endoscopy and occurs approximately once a week in the coordinating study centre (Helios Kliniken Schwerin, Germany). It is therefore expected that 90 patients in five study centres will be reached over a period of 12 months. An interim analysis of the recruited patient number will be conducted after 6 months. If necessary, further study centres must be included to achieve enough participants to reach the target sample size.

## Assignment of interventions: allocation

### Sequence generation {16a}, concealment mechanism {16b}, and implementation {16c}

For randomization, computer-generated random number sequences are generated at the study centre in Schwerin, with odd numbers representing experimental therapy (ET), bipolar electrical haemostasis forceps (HemoStat/Pentax), and even numbers representing standard therapy (ST). Randomization will be performed in blocks of 4 and stratified per centre. Trained study nurses will prepare sealed envelopes and distribute them to the participating centres. Patients meeting the inclusion criteria will be randomized 1:1 during endoscopy, as ascertained by opening the sealed envelopes. Randomization will be performed by the treating endoscopist. The following rules will be applied: the person who prepares the envelopes and conducts the allocation is not involved in the study. The letters are numbered consecutively and are not transparent. The person who opens the letter is not the same person who has prepared the envelopes (endoscopy assistant) [13].

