## Assignment of interventions: blinding

### Who will be blinded {17a}

The study participants will be blinded after being assigned to the interventions. The endoscopic haemostatic method is performed under short sedation (usually propofol sedation). Therefore, the assignment to the intervention cannot be observed by the study participants. Furthermore, the participants are not informed on the assigned treatment arm until the end of the follow up-period of 30 days. The endoscopist cannot be blinded, as he must be aware of which endoscopic intervention he is performing on the patient. Physicians on the ward are not blinded as the endoscopic report will comprise the assigned intervention. On the other hand, outcome assessors will be blinded.

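### A single fixed block size of 4 within each centre lets an informed, unblinded endoscopy team deduce up to about 30% of allocations, and the section conflicts on who conducts the allocation

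*Protocol article*

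**What the plan says.** Section Sequence generation {16a}, concealment mechanism {16b}, and implementation {16c} gives one block size: "Randomization will be performed in blocks of 4 and stratified per centre". On timing it says: "Patients meeting the inclusion criteria will be randomized 1:1 during endoscopy, as ascertained by opening the sealed envelopes". The envelopes are sealed, not transparent and numbered in order.

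Four statements in that section concern who does what:

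- "Trained study nurses will prepare sealed envelopes and distribute them to the participating centres"
- "Randomization will be performed by the treating endoscopist"
- "the person who prepares the envelopes and conducts the allocation is not involved in the study"
- "The person who opens the letter is not the same person who has prepared the envelopes (endoscopy assistant"; the last two words stand in brackets at the end of the sentence.

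Section Who will be blinded {17a} adds: "The endoscopist cannot be blinded, as he must be aware of which endoscopic intervention he is performing on the patient". Ward physicians are not blinded either; outcome assessors are said to be.

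Two other sections matter. Eligibility criteria {10} admits Forrest I a or I b bleeding and excludes Forrest II a to c and III, a distinction made by looking through the endoscope. Outcomes {12} has the endoscopist decide, yes or no, whether primary haemostasis was achieved within 15 minutes.

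**The concern.** In a fixed block of 4 with two patients per arm, the last allocation is always known to anyone who has followed the block, and the third is sometimes known. Stratifying by centre makes the block easy to follow, because all earlier allocations in it were made at that same centre. The treating team is unblinded, and the published protocol discloses the block size.

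The decision that a lesion is oozing, and so eligible, is made in the same session, just before the envelope is opened. If the team already knows the next arm, an easier or harder lesion can be let in or passed over according to that arm. Blinding patients or later assessors does not undo selection at entry. The first component of the primary endpoint is in any case scored by the unblinded endoscopist.

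Separately, if the text does not settle who conducts the allocation and who opens the envelope, centres may do it differently, and none can be audited against a clear rule.

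**Working it through.** **Inputs.** Block size 4, 1:1 allocation (section {16a} to {16c}); 90 patients in five centres (Recruitment {15}). The protocol gives no figure for predictability, so there is none to reproduce. Equal centres are my assumption: 90 / 5 = 18 each.

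**One complete block.** There are 6 equally likely orders of two ET and two ST. For an observer who knows the block size and the allocations so far:

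| Position | Probability that it is certain | Best-guess success |
|---|---|---|
| 1 | 0 | 1/2 |
| 2 | 0 | 2/3 |
| 3 | 1/3 (first two were the same arm) | 1/3 × 1 + 2/3 × 1/2 = 2/3 |
| 4 | 1 | 1 |
| Sum | 4/3 | 17/6 |

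Certain: (4/3) / 4 = 33.3%. Best guess: (17/6) / 4 = 70.8%, against 50% without blocking.

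**This trial.** Eighteen patients are four complete blocks plus two patients (positions 1 and 2 of a fifth block).

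- Certain per centre: 4 × 4/3 + 0 = 5.33. Over five centres: 26.7 of 90 = 29.6%.
- Best guess per centre: 4 × 17/6 + (1/2 + 2/3) = 12.5 of 18 = 69.4%.

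With 5 to 10 centres of near-equal size, the certain share lies between 26.7% and 31.1%.

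**What varying the block size would do.** Simulation at 18 patients per centre, with an observer who knows the set of possible sizes but not the size of the current block:

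| Block sizes | Certain | Best guess | Predictable with over 80% probability |
|---|---|---|---|
| 4 only | about 30% | about 69% | about 30% |
| 2, 4, 6 | about 4% | about 70% | about 48% |
| 4, 6, 8 | about 2% | about 67% | about 19% |

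Blocks of 2 remove certainty but create many near-certain allocations. The mix of 4, 6 and 8 is better on all three measures. No mix removes most of the guessing advantage, so a second safeguard is needed.

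**Possible size of a bias (illustration on an assumption that is not in the protocol).** Suppose selection raises expected success by *d* points in patients known to be going to ET and lowers it by *d* in those known to be going to ST. The bias in the difference is about 0.296 × 2*d*: 3.0 points for *d* = 5 and 5.9 points for *d* = 10. The planned difference is 25.4 points (Sample size {14}).

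**Who allocates.** Side by side, one sentence has the treating endoscopist perform the randomisation. Another places the person who prepares the envelopes and conducts the allocation outside the study. A treating endoscopist is not outside the study, so the two conflict unless performing randomisation and conducting the allocation are different acts, which the text does not say. The preparers are called study nurses, which also sits badly with being outside the study. The bracketed mention of the endoscopy assistant can attach to the opener or to the preparer.

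**The case against.** The predictability figures are upper limits. They require someone who knows the block size, the position in the block and every earlier allocation at the centre. The protocol does not say that one endoscopist treats all cases or that anyone keeps a tally. Eighteen patients per centre in 12 months is about one every three weeks, and an on-call endoscopist may not know the sequence. The article appeared in June 2023, midway through the planned recruitment period of January to December 2023, so block size was public for only part of it. All this stands, and it is why the result is stated as up to about 30%.

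There are safeguards: opaque numbered envelopes, consent before study therapy, and possible adjustment for centre, Forrest class, ulcer size and location (section {20a}). They limit the consequences. They do not prevent deduction from the block, and adjustment cannot reach features of the lesion that are not recorded.

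A reader might infer that the unblinded endoscopist opens the envelope himself. The text does not say so; the assistant opening it is a natural reading. The predictability is the same either way, because both belong to the endoscopy team. A reader might also infer that none of the statements on roles can be reconciled. That is too strong: nurses preparing, an assistant opening and the endoscopist triggering randomisation are compatible, and preparer and opener are already required to differ. The true conflict is narrower: who conducts the allocation, and whether study nurses can count as not involved in the study.

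**Conclusion.** The point holds in a limited form. One fixed block size of 4 per centre, used by an unblinded team at the moment of a judgement-based eligibility decision, lets a fully informed observer deduce up to about 30% of allocations and guess about 69% correctly. A reader might carry the one-third figure for complete blocks straight over to 30 of 90 patients. That is too high here, because each centre of 18 ends with an incomplete block.

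The result assumes equal centres, a known block size and shared knowledge of past allocations within a centre. That the endoscopist decides eligibility is inferred from the Forrest criterion and from randomisation during endoscopy, not stated. The documents show an opportunity for selection; they do not show that any occurred.

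The wording on who conducts the allocation is contradictory as it stands and needs reconciling. The change is advisable and cheap.

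**What to change.** 1. From the next block boundary at each centre, replace the remaining list with randomly varying block sizes, without blocks of 2 (for example 4, 6 and 8), and do not disclose the sizes to the centres.
2. Require eligibility, Forrest class and time to be written on the numbered envelope before it is opened. This commits the judgement first and leaves an audit trail; it addresses the guessing that varying blocks leave behind.
3. Rewrite the section so that one named role outside the treating team prepares the envelopes and one named role, the endoscopy assistant, opens them. Remove or reconcile the two statements on who performs randomisation and who conducts the allocation.

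Cost: new lists and envelopes, no extra staff, and slightly looser balance within a centre (the largest possible imbalance within a block rises from 2 to 4 patients when a block of 8 is used).

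If recruitment has ended, items 1 and 2 no longer apply. Correct the wording to describe what was done, and report the fixed block size as a limitation.

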## Assignment of interventions: blinding

### Who will be blinded {17a}

The study participants will be blinded after being assigned to the interventions. The endoscopic haemostatic method is performed under short sedation (usually propofol sedation). Therefore, the assignment to the intervention cannot be observed by the study participants. Furthermore, the participants are not informed on the assigned treatment arm until the end of the follow up-period of 30 days. The endoscopist cannot be blinded, as he must be aware of which endoscopic intervention he is performing on the patient. Physicians on the ward are not blinded as the endoscopic report will comprise the assigned intervention. On the other hand, outcome assessors will be blinded.

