#### Primary outcome measure

Success of primary haemostasisPeriod: 15 min from localization of the source of bleeding until haemostasisMethod of measurement: assessment by endoscopist: yes/noExplanation: variable of immediate effectivenessNumber of recurrent haemorrhages within 30 daysPeriod: 30 days after initial haemostasisMethod of measurement: evidence of recurrent gastrointestinal bleeding on oesophagogastroduodenoscopy or clinical signs of upper gastrointestinal bleeding (such as tarry stools) and an associated drop in haemoglobin of > 1 g/dl or 0.62 mmol/lExplanation: variable of sustained efficacy in an appropriate observation period, as recurrent bleeding is not uncommon after endoscopic haemostasis

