## Data collection and management

### Plans for assessment and collection of outcomes {18a}

All data collected as part of the study will be documented on a standardized paper-based case report form (CRF) version 2.2 (03/12/2022) (Additional file 1). The investigator is responsible for ensuring that all parts of the CRFs are completed correctly. Errors made in completing the CRFs should be crossed out single-spaced in accordance with ICH-GCP [14] so that the original entry remains legible; the new entry should be dated and initialled with the investigator’s name. In the case of self-explanatory corrections (e.g. numerical error in the date), the justification may be omitted. Each CRF must be signed at least once by the investigator. The completed pages of the CRF will be sent to the lead study centre. A copy will remain at the study centre.

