### Plans to promote participant retention and complete follow-up {18b}

Study participants will be informed and must provide written consent to be contacted by telephone or in writing by the investigator after 30 days to complete follow-up data. A separate list will be provided for participants who cannot be contacted after 30 days or who have deviated from the intervention protocols.

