### Composition of the data monitoring committee, its role and reporting structure {21a}

N/A. A data monitoring committee is not planned, as there will be only one follow-up interview after 30 days asking about rebleeding.

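### The blanket statement that outcome assessors are blinded is untrue for primary haemostasis, which the unblinded endoscopist scores; for 30-day rebleeding, blinding is neither contradicted nor assigned to anyone

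*Protocol article*

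**What the plan says.** Section {17a} of the protocol article describes blinding group by group. Patients are sedated during the procedure and are not told their arm until day 30. For the operator it says "The endoscopist cannot be blinded, as he must be aware of which endoscopic intervention he is performing on the patient". For the wards it says "Physicians on the ward are not blinded as the endoscopic report will comprise the assigned intervention". It then closes with "On the other hand, outcome assessors will be blinded". No assessor is identified and the statement is not limited to any outcome.

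The Objectives section makes the primary endpoint a composite of initial haemostasis and freedom from rebleeding over 30 days. The section on the primary outcome measure has two parts:

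- **Haemostasis** within 15 minutes of locating the source is a yes/no judgement by the endoscopist.
- **Rebleeding** is defined by repeat endoscopy, or by clinical signs together with a haemoglobin drop of more than 1 g/dl. No assessor is named.

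On follow-up, section {18b} has patients "contacted by telephone or in writing by the investigator after 30 days to complete follow-up data", and section {21a} adds that "there will be only one follow-up interview after 30 days asking about rebleeding". Section {18a} says "The investigator is responsible for ensuring that all parts of the CRFs are completed correctly". Section {22} has the investigator judge whether each adverse event is related to the intervention.

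**The concern.** Whether bleeding has stopped within 15 minutes is partly a matter of judgement, above all in oozing (Forrest I b) lesions, which the eligibility criteria admit. The person judging knows the arm and has just applied the device. A haemostasis failure is by itself a failure of the composite, so this judgement feeds straight into the primary analysis. A reader who takes the blinding statement at face value would credit the superiority comparison with a protection that its larger component does not have.

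For rebleeding the issue is different and smaller: the document promises blinded assessment but does not show who provides it.

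**Working it through.** **1. The statements side by side.**

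| Outcome | Who assesses it | Is that person blinded? |
|---|---|---|
| Primary haemostasis | Endoscopist (primary outcome section) | No, by {17a} |
| 30-day rebleeding | Not named; the investigator makes the contact ({18b}) | Not stated beyond the general sentence in {17a} |
| Success of crossover (secondary) | Endoscopist | No, by {17a} |

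The first row cannot be reconciled with an unqualified claim that assessors are blinded. The second row can: a blinded classifier of rebleeding is compatible with everything written.

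**2. How much of the planned difference is at stake.** The inputs come from the sample size section: haemostasis 90% and rebleeding 5% with the forceps, 72% and 16% with standard therapy.

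- Composite, forceps: 0.90 × 0.95 = 0.855, as stated.
- Composite, standard: 0.72 × 0.84 = 0.6048. The article states 60.1%.
- Difference: 0.855 − 0.6048 = 0.2502, so 25.0 points against the stated 25.4. The split below uses 25.0 because it must add up from the component rates.

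The split depends on the convention:

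| Convention | Haemostasis | Remainder | Haemostasis share |
|---|---|---|---|
| Failures counted in sequence | 0.28 − 0.10 = 18.0 points | 0.72 × 0.16 − 0.90 × 0.05 = 7.0 points | 72% |
| Change haemostasis only, rebleeding at 5% | 0.18 × 0.95 = 17.1 points | 7.9 points | 68% |
| Change haemostasis only, rebleeding at 16% | 0.18 × 0.84 = 15.1 points | 9.9 points | 60% |

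On every convention the component scored unblinded carries most of the planned effect.

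**3. The plan's sample size.** With the stated 60.1% and 85.5%, the unpooled two-sided normal formula returns 45 per arm, and exact enumeration of the uncorrected Pearson test at 45 per arm gives 80.0% power. The stated figure reproduces, and the blinding question does not alter it.

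**4. Illustration of the possible bias, on assumptions that are not in the documents.** Suppose both arms truly have 72% haemostasis and 16% rebleeding. Let the endoscopist record a share f of true failures as successes in the forceps arm only, and let c be the chance that such a patient is later counted as a rebleed. Observed success is then 0.6048 in the standard arm and 0.6048 + 0.28 × f × (1 − c) in the forceps arm. Two-sided rejection rates by exact enumeration of Pearson's test, 45 per arm:

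| f | c = 16% | c = 50% | c = 100% |
|---|---|---|---|
| 0 | 4.9% | 4.9% | 4.9% |
| 20% | 7.6% | 5.9% | 4.9% |
| 30% | 11.0% | 7.1% | 4.9% |
| 50% | 22.6% | 10.9% | 4.9% |

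With c = 16% the false differences are 4.7, 7.1 and 11.8 points. That column treats patients whose bleeding never stopped as no more likely to be counted as rebleeding than true successes. It is the unfavourable end of the range shown.

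**The case against.** The operator cannot be blinded, and the article says so openly, in the same paragraph as the disputed sentence. The phrase that introduces that sentence can be read as meaning assessors other than the endoscopist and the ward physicians. This limits the point to wording, but does not remove it: the primary outcome section makes the endoscopist an outcome assessor, and {17a} makes no exception.

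A reader might go further and infer that rebleeding, and so the whole primary endpoint, is assessed unblinded. The document does not support that. It says that an investigator contacts the patient, not that this person knows the arm, was at the endoscopy or classifies the event. The patient is blinded to day 30, and the clinical route to a rebleed needs a measured haemoglobin drop; both limit bias. Operational detail of this kind may also sit in the full protocol or the case report form, which are not shown. What remains is that the article names no blinded assessor and gives the neighbouring tasks to one role.

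A reader might also take the rejection rates as the trial's actual error rate. They are not. The misclassification shares, their restriction to one arm and the chance of later detection are all assumed, and the excess disappears if every false success is later caught as rebleeding.

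**Conclusion.** The sentence on blinded assessors is wrong as written for primary haemostasis and should be corrected. This follows from the text alone. That this component supplies about 60 to 72% of the planned difference rests on the plan's assumed rates and on the way the difference is split.

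For rebleeding the finding is only that no blinded assessor is identified.

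The size of any bias cannot be derived from the documents. As an illustration, if 20 to 50% of true forceps-arm failures were called successes, two-sided rejection under no true difference would be about 7.6 to 22.6% if these patients rebleed at 16%, 5.9 to 10.9% if half are later caught, and 4.9% if all are. Sample size, test and endpoint definition need not change.

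**What to change.** - Replace the sentence in {17a} with a statement that primary haemostasis is judged by the unblinded endoscopist and that blinded assessment applies only to 30-day rebleeding.
- Have an existing team member who was not at the endoscopy make the 30-day contact and classify rebleeding by the criteria already in the primary outcome section, without access to the allocation or the endoscopy report.
- Report haemostasis and rebleeding separately beside the composite. The outcomes section already lists them as separate measures, so this mainly makes explicit what is there.
- Optionally, count a recorded start of crossover or rescue treatment as a haemostasis failure, as a classification check only. The same unblinded endoscopist decides on crossover, so this does not remove the bias.

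The cost is a change of wording and the reassignment of one contact per patient, with no extra reader and no extra patients. The price for the trial is to concede that most of its planned effect rests on an unblinded judgement.

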### Procedure for unblinding if needed {17b}

In the case of a life-threatening emergency, both the patient and subsequent clinicians are unblinded if information about the treatment group is necessary (e.g. the fact whether clips are present or not).

## Data collection and management

### Plans for assessment and collection of outcomes {18a}

All data collected as part of the study will be documented on a standardized paper-based case report form (CRF) version 2.2 (03/12/2022) (Additional file 1). The investigator is responsible for ensuring that all parts of the CRFs are completed correctly. Errors made in completing the CRFs should be crossed out single-spaced in accordance with ICH-GCP [14] so that the original entry remains legible; the new entry should be dated and initialled with the investigator’s name. In the case of self-explanatory corrections (e.g. numerical error in the date), the justification may be omitted. Each CRF must be signed at least once by the investigator. The completed pages of the CRF will be sent to the lead study centre. A copy will remain at the study centre.

### Plans to promote participant retention and complete follow-up {18b}

Study participants will be informed and must provide written consent to be contacted by telephone or in writing by the investigator after 30 days to complete follow-up data. A separate list will be provided for participants who cannot be contacted after 30 days or who have deviated from the intervention protocols.

